### 7.5.2. Prohibited concomitant medication

Subjects are prohibited from receiving the following therapies during the Screening and Treatment Phase (including retreatment for post-complete response relapse) of this trial:

- Anti-cancer systemic chemotherapy or biological therapy
- Chemotherapy not specified in this protocol
- Immunotherapy not specified in this protocol
- Investigational agents other than Avelumab and Regorafenib
- Live vaccines within 30 days prior to the first dose of trial treatment and while participating in the trial. Examples of live vaccines include, but are not limited to, the following: measles, mumps, rubella, varicella, zoster, yellow fever, intranasal influenza, rabies, BCG and typhoid vaccine.
- Current use of immunosuppressive medication, EXCEPT for the following:
  - Intranasal, inhaled, topical steroids, or local steroid injection (e.g., intra-articular injection);
  - Systemic corticosteroids at physiologic doses  $\leq 10$  mg/day of prednisone or equivalent; Higher doses can be used for the management of immune related adverse events and/or skin rash (see appendix 8).
  - Steroids as premedication for hypersensitivity reactions (e.g., CT scan premedication).
- The use of oral anticoagulation therapy (i.e. warfarin, acenocoumarol, phenprocoumon) is not permitted since warfarin is metabolized by CYP2C9 and CYP3A4. Low molecular weight heparin and heparin are allowed.

Subjects who, in the assessment by the investigator, require the use of any of the aforementioned treatments for clinical management should be removed from the trial. Subjects may receive other medications that the investigator deems to be medically necessary.

The Exclusion Criteria describes other medications which are prohibited in this trial.

There are no prohibited therapies during the Post-Treatment Follow-up Phase.

*Short course Radiotherapy* for symptoms or *palliative* treatment may be allowed after discussion with the sponsor.

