### 7.6.2. Management of Adverse Events

Any toxicity observed during the course of the study could be managed by interruption and/ or dose reduction of the dose if deemed appropriate by the Investigator. Dose adjustments are to be made according to the greatest degree of toxicity (please refer to the IMP Investigator's Brochure), and in accordance with table below:

| Level       | -1        | 1          | 2          |
|-------------|-----------|------------|------------|
| Avelumab    | 10 mg/kg  | 10 mg/kg   | 10 mg/kg   |
| Regorafenib | 80 mg x 1 | 120 mg x 1 | 160 mg x 1 |

Adverse events will be graded using the NCI Common Terminology Criteria for Adverse Events Version (CTCAE) v5.0.

The following guidelines outline dose adjustments for the most frequent of these toxic effects. If any severe toxicity occurs it should be referred to the principal investigator in order to decide management in the best interest of the patient. If a patient experiences several adverse events with conflicting recommendations, please use the dose modification recommendation that reduces the dose to the lowest level.

Once a dose has been reduced, it will in no case be increased again.

For all cohorts except cohort [A'], patients requiring a delay of > 4 weeks OR > one dose reduction (of Regorafenib) if RP2D is 120mg of Regorafenib and > 2 dose reductions if RP2D is 160mg of Regorafenib should permanently discontinue regorafenib. Note that further treatment by avelumab monotherapy will be allowed until disease progression, unacceptable toxicity, etc. (see section 3.2.2 for more details).

For cohort [A'], regorafenib should be interrupted and no dose reduction are allowed. Patients requiring a delay of > 4 weeks should permanently discontinue regorafenib. Note that further treatment by avelumab monotherapy will be allowed until disease progression, unacceptable toxicity, etc. (see section 3.2.2 for more details).

Patient should go off study if regorafenib has been permanently discontinued before first dose of avelumab.

Please refer to Appendix 7 and 8 and to most updated Investigator Brochure for management of toxicities.

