## APPENDIX 8: DOSE DELAYS FOR TOXICITIES RELATED TO AVELUMAB AND REGORAFENIB INCLUDED IMMUNE-RELATED TOXICITIES

| Hand-foot skin reactions
Except for irAE skin reaction                                                                                                                                         | Regorafeniba
Management/Dose-modification                                                                                                                                                                                                                                                                                                                                                                                                               | Avelumab
Management/Dose-modification |
|----------------------------------------------------------------------------------------------------------------------------------------------------------------------------------------------------------|------------------------------------------------------------------------------------------------------------------------------------------------------------------------------------------------------------------------------------------------------------------------------------------------------------------------------------------------------------------------------------------------------------------------------------------------------------------------------|-------------------------------------------------|
| Grade 1: Numbness, dysesthesia, paraesthesia, tingling, painless swelling, erythema or discomfort of the hands or feet which does not disrupt the patient's normal activities.                    | Any: Maintain dose level and immediately institute supportive measures for symptomatic relief.                                                                                                                                                                                                                                                                                                                                                                        | No dose modification                            |

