|                                                                                                     |                                                                                                                                                                                                                                                                                                                                                                                                                                             | Initial Management                                                                                                                                                                                                                                                  | Follow up Management                                                                                                                                                                                                                                                                                                                                                                           |
| Grade 1 to 2
Covering ≤ 30% body surface area                                                    | 
No change
 
Consider skin biopsy and dermatology consult
 
Consider 1.0 mg/kg/day prednisone or equivalent (max 1 week, taper steroids included) and/or dermocorticoids
 
In case of fever, consider infectious etiology in case of pruritus, add antihistamine
                                                                                                                                                       | Continue avelumab therapy
Symptomatic therapy (for example, antihistamines, topical steroids)                                                                                                                                                                    | 
If Grade 2 persists > 1 to 2 weeks or recurs:
Withhold Avelumab therapy
Consider skin biopsy
Consider 0.5 - 1.0 mg/kg/day prednisone IV or equivalent
One improving, taper steroids over at least 1 month, consider prophylactic antibiotics for opportunistic infections, and resume Avelumab therapy following steroid tapers
If worsen: treat as grade 3 to 4
 |

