| Grade 3 to 4
Grade 3: Covering ≥ 30% body surface area
Grade 4: life threatening consequences | 
Delay until ≤ grade 2 and reduce 1 dose level for grade 3
 
Consider skin biopsy and dermatology consult
 
Consider 1.0 mg/kg/day prednisone or equivalent (max 1 week, taper steroids included) and/or dermocorticoids
 
In case of fever, consider infectious etiology in case of pruritus, add antihistamine
 
Permanently discontinue for grade 4, recurrent grade 3 or in case of no recovery after 4 weeks
 | 
Withhold for grade 3
Permanently discontinue for grade 4 or recurrent grade 3
Avelumab
Consider skin biopsy, Dermatology consult
1.0 to 2.0 mg/kg/day prednisone or equivalent
Add prophylactic antibiotics for opportunistic infections
 | 
If improves to grade ≤1: taper steroids over at least 1 month,
Resume Avelumab therapy following steroid tapers (for initial grade 3)
                                                                                                                                                                                                                                               |

a For cohort [A], regorafenib should be interrupted and no dose reduction are allowed. Patients requiring a delay of > 4 weeks should permanently discontinue regorafenib

| Pneumonitis (NCI-CTCAE v5.0)                                                                        | Regorafenib             | Avelumab                                                                                                                                                                                                                                                                       |                                                                                                                                                                                                                                                                                                 |

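### For a Grade 3 to 4 rash in a patient on both drugs, the regorafenib and avelumab columns of the Appendix 8 Rash table set systemic steroid durations that cannot both be followed.

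*Protocol*

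**What the plan says.** Appendix 8 has a single table for rash, with one row per grade band, one regorafenib column and two avelumab columns (initial and follow-up management).

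In the Grade 3 to 4 row:

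- **Regorafenib column:** "Consider 1.0 mg/kg/day prednisone or equivalent (max 1 week, taper steroids included) and/or dermocorticoids".
- **Avelumab, initial management:** "1.0 to 2.0 mg/kg/day prednisone or equivalent". Avelumab is withheld for Grade 3 and stopped permanently for Grade 4 or recurrent Grade 3.
- **Avelumab, follow-up management:** "If improves to grade ≤1: taper steroids over at least 1 month". After an initial Grade 3 rash, avelumab resumes once the taper is finished.

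Section 7.3 plans both drugs for every cohort, with avelumab every two weeks from Cycle 1 Day 15. Section 7.6.1 requires permanent discontinuation of avelumab when two or more infusions in a row have to be cancelled.

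**The concern.** Both columns address the same event in the same patient, and both instruct on systemic steroids. In the other Appendix 8 tables that give steroid doses under drug-specific columns (liver enzymes, diarrhoea and colitis, pneumonitis, endocrine disorders, creatinine, other immune-related events), the steroid instruction stands only under avelumab. The Rash table is the one place where regorafenib has its own, and it differs.

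Two things are at stake. The first is how long a patient with a severe rash is immunosuppressed; section 11.4 makes rash of Grade 3 or higher reportable as a serious adverse event. The second is avelumab exposure, because resumption is tied to the end of the taper. Two investigators who each follow a written instruction could treat the same rash differently.

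**Working it through.** The plan gives no figure to reproduce here, so the check compares the cells and searches for a rule that decides between them.

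**1. Duration.** Inputs come from the Grade 3 to 4 row of the Rash table.

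- Regorafenib cell: total course, taper included, ≤ 7 days.
- Avelumab cells: total course = treatment until grade 1 or less + taper, with taper ≥ 1 month. Counting a month as 28 to 31 days, total ≥ 28 days even if the first part is set to zero.
- A course of ≤ 7 days and a course of ≥ 28 days do not overlap. The bounds differ by a factor of at least 28 / 7 = 4.

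**2. Dose.** The regorafenib cell gives 1.0 mg/kg/day and the avelumab cell 1.0 to 2.0 mg/kg/day. These meet at one value, so dose alone is a difference and not a strict contradiction. The contradiction lies in duration.

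**3. Search for a deciding rule.**

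| Place | What it covers | Does it decide? |
|---|---|---|
| Rash table headings | Grade band and drug | No statement about suspected cause |
| Hand-foot table heading, Appendix 8 | Carries a carve-out: "Except for irAE skin reaction" | Shows that a split by type of reaction was written elsewhere; the Rash table has none |
| Section 7.5.2 | Permits steroids above the physiologic dose for immune-related events and skin rash | Refers back to Appendix 8 |
| Section 7.6.1 | Work-up of suspected immune-related events, restart and stopping of avelumab | Refers to Appendix 8 for management |
| Section 7.6.2 | "If a patient experiences several adverse events with conflicting recommendations, please use the dose modification recommendation that reduces the dose to the lowest level" | Concerns study-drug dose across several events, not steroid duration for one event |

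None of these decides between the columns.

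**4. Consequence for avelumab after a first Grade 3 rash.** Planned infusions are 14 days apart.

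- Taper of at least 28 days: 28 / 14 = 2, so at least two planned infusions fall within it. The withheld period is longer still, because the taper starts only after improvement to grade 1 or less.
- Course of at most 7 days: 7 / 14 = 0.5, so no planned infusion or one falls within it.
- Section 7.6.1 sets its stopping rule at two consecutive cancellations, which is the number of planned infusions that the shortest permitted taper spans. The protocol does not say whether an infusion withheld during a taper counts as cancelled. The Rash table says to resume after the taper. The two texts need to be read together and made consistent.

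**The case against.** The best defence is that each column is meant for rash caused by that drug: a short course for drug rash, a long taper for immune-related rash. Section 7.5.2 names immune-related events and skin rash as separate indications, section 7.6.1 asks for other causes to be ruled out first, and section 11.2.9 wants causality judged for each trial drug. That reading is coherent and may be what was intended. It is not written in the Rash table, and it leaves a rash of unclear cause in a patient on both drugs unassigned.

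Three further points partly stand:

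- The regorafenib cell is permissive. It can be met with topical treatment alone, and an investigator working from the avelumab column need not start the one-week course. The one-week limit is nevertheless explicit once systemic steroids are given under that cell.
- The columns do not always apply together. Avelumab starts on Cycle 1 Day 15, so an earlier rash occurs on regorafenib alone, and either drug may later be continued alone. The conflict is confined to patients on both.
- Section 7.6.2 sends severe toxicity to the principal investigator, and both columns mention a dermatology consult. This gives a route to a decision in the individual case but leaves the conflicting instruction in place.

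It is also true that the missed infusions follow from the avelumab column itself. The regorafenib column never says that avelumab may restart after a week.

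**Conclusion.** The conflict holds for the Grade 3 to 4 row, for a patient on both drugs who is given systemic steroids: at most 7 days in total against a taper alone of at least about 28 days. This rests on the table as written, with no split by cause. The infusion count applies only to a first Grade 3 rash, since Grade 4 and recurrent Grade 3 end avelumab. It is a safety and treatment-exposure ambiguity that should be corrected.

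A reader might infer more than the documents support:

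- *The whole Rash table contradicts itself.* The Grade 1 to 2 row also ends with "One improving, taper steroids over at least 1 month", but that step begins only if Grade 2 lasts beyond one to two weeks or recurs. It can follow a one-week course in sequence.
- *The problem can be sized from the rash rates in sections 1.2.3 and 1.3.3.* Those are single-agent figures without a grade. The protocol gives no Grade 3 or higher rash rate for the combination.
- *The month-long taper forces permanent discontinuation of avelumab.* That depends on whether withheld infusions count as cancelled, which section 7.6.1 does not say.
- *The primary endpoints or decision rules are affected.* Nothing in the document shows this.

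**What to change.** The sponsor's clinical team should reconcile the steroid instructions in the Grade 3 to 4 row of the Rash table. Either of two forms would do:

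- one merged steroid instruction for the row, as the myocarditis table in the same appendix already has for both drugs; or
- a statement of which column governs and when, including for a rash of unclear cause.

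The result should then be checked against section 7.6.1, so that resumption after the taper and the rule on consecutive cancelled infusions agree. It should also be clear whether an infusion withheld during a taper counts as cancelled. Which steroid dose and duration to use is a clinical decision, and none is proposed here.

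The cost is an amendment that rewords one table row, with a matching clarification in section 7.6.1 if the check shows one is needed. Sample sizes, endpoints and analyses do not change.

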## APPENDIX 10: SUMMARY OF THE CHOI CRITERIA

| Response | Definition                                                                                                                                                      |
|----------|-----------------------------------------------------------------------------------------------------------------------------------------------------------------|
| CR       | Disappearance of all lesions
No new lesions                                                                                                                  |
| PR       | A decrease in size $\geq 10\%$ or a decrease in tumour attenuation (HU) $\geq 15\%$ on CT
No new lesions
No obvious progression of non-measurable disease |
| SD       | Does not meet criteria for CR, PR, or PD
No symptomatic deterioration attributed to tumour progression                                                       |
| PD       | An increase in tumour size $\geq 10\%$ and does not meet criteria of PR by tumour attenuation on CT
New lesions                                              |

Abbreviations: CR=complete response; PR=partial response; SD=stable disease; PD=progressive disease; HU=Hounsfield unit.
